#### PAT

All participants, including those in the control arm, will be provided a smart watch in the form of an Apple Watch or Android watch. This PAT device will allow participants to accurately track exercise and total steps each day [48]. The US 2018 Physical Activity Guidelines Advisory Committee Scientific Report found “moderate” to “strong” evidence that mobile phones and wearable devices increase physical activity [49]. Through PAT, users will be able to set daily goals and attain or improve motivation to continue asthma management. For individuals randomized to groups that also include the MES or SA, those programs will incorporate PAT data that are remotely transmitted, to facilitate asthma management motivation. In formative work, AAEAs were enthusiastic regarding interventions that provided users a smart watch, and stated they were much more likely to continue in a trial that did so.

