### Intervention Component Refinement

The MES, SA, and SMS components have been developed in previous work with different patient populations and behavioral targets. The current protocol includes 2 phases. During Phase 1 of the project, all 3 components will be refined and beta-tested for use with AAEAs having uncontrolled asthma. Minor adjustments will be required as we will now be integrating components both alone and in combination. Additionally, component refinement will be achieved with significant input from relevant stakeholders. Stakeholders include AAEAs with asthma, asthma nurses, asthma educators, primary care physicians, asthma specialty physicians, and computer specialists. All content has been developed through multi-step formative work, but it is important to continue to refresh and update content (eg, changing asthma guidelines and social phenomenon). For the primary stakeholder (AAEAs with asthma), 3 focus groups (4-6 individuals per group) will be held; the specifics of each component to be discussed are described below. Finally, prior to evaluation in the trial, beta-testing with a group of 10 AAEAs with asthma will be performed for each component arm to ensure that combinations are acceptable and well-integrated. Beta-testers will be asked to use assigned components, followed by an interview to obtain feedback on content, delivery, and technological issues.

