This study will use a 6-arm incomplete factorial design for the component selection experiment (Table 1). A full factorial design will not be used as some of the experimental combinations cannot be present simultaneously (eg, MES and SA are mHealth and involve human delivery of the same intervention content, and therefore logically cannot be combined), and PAT will be provided to all participants. Byar et al [57] described such incomplete designs, and in particular, we are employing “Design 3,” which is a “2^3^ − Y_AB_ − Y_ABC_” design. This design matches with our experimental combination as MES (A) and SA (B) components cannot occur together. Table 1 shows the incomplete factorial design given the possible combinations of the 4 components [55]. As the full factorial design is not feasible for the current setup, we also considered a 2^3−1^ fractional factorial design with 3 factors but with 4 (2^3−1^) treatment conditions, allowing aliasing of the highest-level interaction (ie, each main effect will be confounded with a 2-factor interaction). However, our design with 6 components is a superset of that 2^3−1^ fractional factorial design and will result in better evaluation of treatment combinations than any fractional factorial (see the study by Byar et al [57]). This design preserves much of the full factorial structure and provides more reasonable results than a fractional factorial design [58]. This design also allows evaluation of the main effect of each component and exploration of interaction effects when components are combined, though more assumptions are needed as a full factorial (=2^3^) is not present. One assumption is a “saturated design” when the combination missing (AB and ABC) is assumed to be 0 or have no effect. The component selection experiment is powered for the main effects and will include 180 participants (or 30 participants per arm).

**Table 1 table1:** Intervention conditions.

Experimental condition	Motivational Enhancement System	SMS text messaging	Supportive accountability	Usual care	Physical activity tracking
1	Yes	No	No	No	Yes
2	No	Yes	No	No	Yes
3	No	No	Yes	No	Yes
4	Yes	Yes	No	No	Yes
5	No	Yes	Yes	No	Yes
6	No	No	No	Yes	Yes

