### Statistical Analysis

We will initially characterize the data heterogeneity and frequency distributions of asthma control, the primary outcome, and all secondary outcomes (asthma management and IMB/SRT constructs). We will check for out-of-range values, outliers, and abnormal values using graphical methods and create descriptive summaries to ensure that all values are within expected ranges. Unexpected findings will prompt checking of raw data for accuracy of data entry and recording. We will analyze the effect of the intervention components on the longitudinal measures of asthma control (ACT) using a mixed effects linear model for repeated measures analysis of variance (ANOVA) of a factorial design. This model will include a fixed effects indicator for each intervention component (SA, MES, TXT, and PAT) and time, along with all interactions with time. Random intercepts will be used to account for the longitudinal nature of the data. Before evaluating which components contribute to a potential change in the ACT score, we will use the model to compare the treatment with all 3 components and the control condition to determine whether the complete intervention is efficacious. If this statistical test is significant, we will identify those components that result in a significant change in the ACT score by examining the interactions between the main effects and time using the strategy advocated by Collins et al [53], which begins with the simplest effects and only adds higher-order interactions if needed. We will use a *P* value of <.05 for the test of total effect (difference between the treatment with all 3 components and the control treatment) and .1 to identify which components contribute to the total effect. We will use a higher threshold for the component selection test because we want to reduce the likelihood of not selecting a component that is contributing to the total effect. Secondary outcomes will be analyzed using a similar approach, but they are not powered. If significant baseline group imbalance is detected for any variable and its correlation with the outcome is 0.30, that variable will be included as a covariate in the inferential analyses. Dropouts and completers will also be compared in terms of baseline variables.

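### The gate for component selection tests a three-component package that no arm receives and that the protocol says cannot be delivered

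*Protocol article*

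**What the plan says.** Before looking at single components, the Statistical Analysis section uses the longitudinal model to "compare the treatment with all 3 components and the control condition to determine whether the complete intervention is efficacious". The threshold is P "<.05 for the test of total effect (difference between the treatment with all 3 components and the control treatment". The next step is conditional: "If this statistical test is significant, we will identify those components that result in a significant change in the ACT score". Components are then tested at .1, a looser level chosen so that contributing components are not missed.

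Other sections identify the three components. Intervention Component Refinement begins: "The MES, SA, and SMS components have been developed in previous work with different patient populations and behavioral targets". It then says that "all 3 components will be refined and beta-tested". Physical activity tracking (PAT) does not vary between arms: "All participants, including those in the control arm, will be provided a smart watch".

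Study Trial Design states that "MES (A) and SA (B) components cannot occur together", because they deliver the same content, one by app and one by a nurse. It declares that the two missing combinations (MES with SA, with or without TXT) are handled by setting their terms to zero. It also says that the experiment is powered for main effects. Table 1 lists six conditions, all with PAT: MES; TXT; SA; MES+TXT (arm 4); SA+TXT (arm 5); usual care (arm 6).

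**The concern.** The gate contrast matches no row of Table 1 and names a combination that the protocol itself rules out. It exists only as a sum of three model coefficients. That sum credits the package with the full MES effect plus the full SA effect, although the two deliver the same content. No arm can check this.

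Two things are at stake. First, a significant gate would be reported as efficacy of a complete intervention that nobody received. Second, a non-significant gate stops component selection, which is the purpose of the experiment, and the sum is estimated much less precisely than the components behind it.

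**Working it through.** **Reproducing the plan's figure.** 150 × 1.2 = 180 = 6 × 30, as stated. The 150 cannot be rebuilt, because the article gives no effect size, SD or power. Completers per arm are 24 (180 × 0.8 / 6) or 25 (150 / 6). The range 24 to 30 is used below.

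**Matching the gate to the arms.**

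- Three components read as MES, SA and TXT: no arm.
- Three components counting PAT: arms 4 and 5 both qualify, neither is named, and control also has PAT. If arm 4 versus 6 were meant and only SA worked, the gate would pass about 5% of the time, because SA is not in the contrast.

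**Precision.** Take the additive model with n per arm and SD σ. MES and SA are each compared with the arms that have neither, using two arms per side. TXT compares three arms with three.

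- Var(MES) = Var(SA) = σ²(1/2n + 1/2n) = σ²/n
- Cov(MES, SA) = σ²/2n, from the shared comparison arms
- Var(TXT) = σ²(1/3n + 1/3n) = 2σ²/3n, uncorrelated with the other two
- Var(MES+SA+TXT) = (σ²/n)(1 + 1 + 2 × 0.5 + 2/3) = 11σ²/3n

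At n = 24 the standard errors in SD units are 0.204 (MES or SA), 0.167 (TXT) and 0.391 (gate). The gate's ratio is √(11/3) = 1.91 to MES or SA, and √(11/2) = 2.35 to TXT. Both n and σ cancel. Repeated measures change the effective SD but not these ratios.

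**Power without an assumed SD.** A main effect with 80% power at two-sided .10 has a standardised size of 1.645 + 0.842 = 2.487. If only that component works, the gate's standardised size is 2.487/1.915 = 1.299 for MES or SA, and 2.487/2.345 = 1.060 for TXT. At two-sided .05 the gate's power is P(Z > 1.960 − 1.299) = 25%, or P(Z > 1.960 − 1.060) = 18%.

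**Range over assumed effects.** One active component, normal approximation, two-sided tests, 24 to 30 per arm. Blocked means the component passes its own test but the gate fails.

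| Effect | Gate passes | Component's own .10 test | Component successes blocked |
|---|---|---|---|
| 0.3 SD | 12–14% | 43–64% | 74–83% |
| 0.5 SD | 25–30% | 79–96% | 66–73% |
| 0.75 SD | 48–57% | 98–100% | 42–52% |
| 1.0 SD | 73–82% | about 100% | 18–27% |

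As an illustration in Asthma Control Test (ACT) points, take a single 3-point effect at 25 per arm with an assumed SD of 3, 4, 5 or 6. The gate passes in 74%, 50%, 35% or 26%.

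**Replacement test.** A joint test of MES = SA = TXT = 0 at one time point has 3 df. At 24 per arm and 0.5 SD the noncentrality is:

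- MES or SA alone: 24 × (4/3) × 0.25 = 8
- TXT alone: 24 × 1.5 × 0.25 = 9
- MES and SA together: 24 × (4/3) × (0.25 + 0.25 − 0.25) = 8
- TXT with MES, with SA, or with both: 8 + 9 = 17

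| Working components (0.5 SD each, 24 per arm) | Gate as written | Joint test |
|---|---|---|
| One | 25% | 65% (MES or SA), 71% (TXT) |
| MES and SA | 73% | 65% |
| TXT and one of MES or SA | 73% | 95% |
| All three | 97% | 95% |

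**The case against.** Four points can be made for the plan.

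- **The assumption is declared.** Study Trial Design says that extra assumptions are needed and sets the missing terms to zero, and Statistical Analysis calls the comparison model-based. A reader might infer a hidden extrapolation, and the text does not support that. But the declaration only makes the sum estimable. It does not make the package deliverable, and zero interaction is hard to defend for two deliveries of the same content.
- **The power loss depends on the scenario.** A reader might infer that the gate blocks most single-component successes, or that an effective component would usually never be examined. The documents give no SD or effect size to support either statement. With one active component, the share blocked falls to about half at 0.75 SD and to 18–27% at 1.0 SD. If several components work additively the gate does well. MES and SA are also matched in content, so both may work or neither. This objection stands.
- **The joint test has costs.** It is weaker than the present gate if only MES and SA work, and slightly weaker if all three do. It has no direction: a harmful MES effect of 0.5 SD would open it 65% of the time. With only MES active at 0.5 SD, wrongly selecting SA or TXT rises from about 7% to about 16% if no direction is required. These costs stand and shape the fix.
- **The gate protects against false selection.** Without it, three tests at .10 select at least one inert component in about 26% of trials when nothing works, against at most 5% with it. This stands, so the gate should be replaced and not simply removed.

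**Conclusion.** The structural error holds without any statistical assumption. The gate names a package that is in no arm and that the protocol says cannot exist, so its success could not establish efficacy of a complete intervention. Counting PAT as the third component leaves two candidate arms and no choice between them.

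The loss of precision also holds generally under the additive model: a standard error 1.9 to 2.3 times that of a component, and gate power of about 18% to 25% where a single main effect has 80%. This works against the plan's own reason for testing components at .1.

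The claim that most single-component successes are blocked is conditional. It needs exactly one active component with an effect below about 0.75 SD at 24 to 30 per arm. The percentages rest on two-sided tests, a normal approximation and equal arms.

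**What to change.** Delete the comparison of a three-component treatment with control. Replace it with one joint test at P<.05 that the MES, SA and TXT effects on ACT change are all zero. State the time contrast, because the model has several visits and the test has 3 df only at one time point. If it is significant, select components at .1 as now, but only where the effect is in the beneficial direction. For package efficacy, report arm 4 versus arm 6 and arm 5 versus arm 6 as estimates with confidence intervals.

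This is a wording change to the analysis section and any statistical analysis plan, with no added participants, visits or data. At 24 per arm and 0.5 SD it lowers the pass rate from 97% to 95% if all three components work, and from 73% to 65% if only MES and SA work. It raises it from 25% to 65–71% if one works, and from 73% to 95% if TXT and one of the other two work. The authors should state this trade-off when they adopt the test.

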## Methods

### Study Participants and Setting

Phase 2 consists of a clinical trial study. The study will include 180 AAEAs (30 per arm; N=150 + 20% attrition) aged 18-30 years with persistent asthma that is not fully controlled (defined as a score of less than 19 on the ACT) [35]. We have intentionally chosen uncontrolled asthma patients as the program is designed to help take control of their asthma, and these patients would be the most motivated to use such an intervention. Participants must also own or have access to a cellular phone for the duration of the study and have a primary care physician. Recent data from the Pew Research Center demonstrate that 98% of Black individuals currently own a cellular phone, and that 96% of those aged 18-29 years own a smartphone [36]. To encourage participation, we will pay the cellular bill during the 8-week intervention period for all participants, a strategy that we and others have found to be extremely effective in this population. This will be in addition to the participation incentives. The exclusion criteria will be any other significant cardiopulmonary disease (including chronic obstructive pulmonary disease), a greater than 20 pack-year smoking history (as this level has been associated with the development of chronic obstructive pulmonary disease) [37], developmental delay or mental illness such that participation in the program would not be possible, and pregnancy. Women who become pregnant during the course of the study will be allowed to participate with written approval from their physician. Finally, as PAT will be part of the intervention, any subject who is unable to do mild physical activity for any health reason (including asthma) will be excluded. The ability to participate in mild physical activity will be verified by each participant’s primary care provider.

Participants will be recruited through clinical and community locations. Clinical locations will include the American Lung Association-Airway Clinical Research Centers network, as well as clinics at the University of Michigan, Wayne State University, and Detroit Medical Center. Community locations will utilize online recruitment primarily through social media, using procedures we have developed in previous work [38,39]. All components of the trial (including recruitment, signed informed consent, and intervention education components) will be done remotely.

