#### Randomization

Participants will be randomized to 1 of 6 study arms following baseline. Randomization will be stratified by sex as we expect 65%-70% of subjects to be female (given the demographics of asthma among AAEAs). We will randomize using permuted blocks with sex as a stratification variable. Permuted blocks have the advantage of ensuring a balance between treatment arms for important prognostic variables without unmasking the next treatment allocation [60]. The randomization program/code will be developed and maintained centrally by a biostatistician.

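### The primary model prespecifies neither baseline ACT nor the stratification factor sex, and its rule for adding covariates rests on baseline significance tests that rarely recover the lost precision

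*Protocol article*

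**What the plan says.** All references are to the protocol article.

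- **Randomization:** "We will randomize using permuted blocks with sex as a stratification variable". The reason given is the expected sex mix: "Randomization will be stratified by sex as we expect 65%-70% of subjects to be female".
- **Measurement:** ACT is the primary outcome, and data are collected at baseline and at 3, 6 and 12 months.
- **Statistical Analysis, model:** the fixed effects listed are an indicator per component, time, and interactions with time. "Random intercepts will be used to account for the longitudinal nature of the data". Components are selected on the interactions between their main effects and time, at a threshold of 0.1. No sex term, baseline ACT covariate or constraint on baseline means is listed.
- **Statistical Analysis, covariates:** the one stated route into the model is "If significant baseline group imbalance is detected for any variable and its correlation with the outcome is 0.30", in which case the variable is added to the inferential analyses.
- **Study Participants and Setting:** entry requires an ACT score below 19, so the baseline range is cut off.

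**The concern.** Three features of the stated plan work against precision.

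- **Baseline ACT.** A component effect that is free at baseline turns each component-by-time term into a difference in change scores. Under randomization the expected baseline means are equal, and using that fact, by adjustment or constraint, gives a smaller variance.
- **The covariate rule.** In a randomized trial a significant baseline imbalance is a chance event. The rule therefore admits variables by chance and passes over prognostic variables that happen to be balanced. As printed it also cannot be applied: the value 0.30 has no direction, the visit at which the outcome is correlated is not named, and no test level is given.
- **Sex.** It is important enough to stratify on, but it is not in the model. Because stratified blocks keep it balanced, the imbalance rule would almost never bring it in.

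At stake is the chance of detecting a useful component in a trial with 30 participants per arm.

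**Working it through.** **The plan's own figure.** 6 × 30 = 180, and 150 × 1.20 = 180, so the total reproduces. No power, effect size, SD or correlation is printed, so the planned precision cannot be reproduced. The correlations, SDs and sex effects below are assumptions, shown as ranges.

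**1. Gain from baseline ACT, equal visit variances.** Let rho be the correlation between baseline and 3 months, with unit variance at each visit.
- Change-score variance: 2(1 − rho).
- Baseline-adjusted variance: 1 − rho².
- Ratio: (1 − rho²) / [2(1 − rho)] = (1 + rho)/2.
- rho = 0.4 gives 0.70, 0.5 gives 0.75, and 0.6 gives 0.80.

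A generalized least squares calculation for the six arms, four visits and 25 per arm gives the same ratios for MES and TXT.

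**2. Gain from baseline ACT when entry truncates baseline.** Let r be the retest correlation before truncation and k the fraction of baseline variance left after selecting ACT below 19.
- Change-score variance: (1 − r²) + k(1 − r)².
- Adjusted variance: 1 − r².
- Ratio: (1 + r) / [1 + r + k(1 − r)].
- Truncated normal: k = 1 − aλ − λ², with a = (18.5 − mean)/SD and λ = φ(a)/Φ(a). The cut is at 18.5 because scores are taken as whole numbers.
- Mean 17, SD 4: a = 0.375, λ = 0.5755, k = 0.453.
- Mean 19, SD 4: a = −0.125, λ = 0.879, k = 0.337. SD 5 lies between these two values of k.
- r = 0.6, k = 0.453: 1.6/(1.6 + 0.181) = 0.90.
- r = 0.8, k = 0.337: 1.8/(1.8 + 0.067) = 0.96.

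The variance saving is therefore about 4-10%.

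**3. What the imbalance rule does.** With an assumed test level of 0.05 and k independent baseline variables, the chance of at least one flag is 1 − 0.95^k: 0.40 for 10 variables and 0.64 for 20. That covers only the first of the two conditions. A simulation applied both, reading 0.30 as a minimum: 4,000 trials per scenario, 150 analysed, rho 0.5, and 10 baseline variables of which two were prognostic at about 0.4. A variable was added in 8-10% of trials. The empirical SE of the TXT effect was 0.163 SD unadjusted, 0.160 under the rule, and 0.139 with baseline ACT and sex fixed in the model. Rejection under the null was 0.097-0.104 against 0.10 when sex did not affect change. This favours the rule, since added variables were allowed to act on change.

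**4. A covariate added without a time interaction.** With complete visits and random intercepts, a time-invariant covariate shifts all four visits of a participant equally and cancels from within-person change. A numerical check with a deliberately imbalanced prognostic covariate left the component-by-time estimates unchanged to about 1e-16.

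**5. Sex.** If sex shifts only the ACT level, it cancels in the same way: the SE was 0.163 with and without it. If sex shifts change by d (in SD units, change variance 1), leaving it out inflates the estimated SE by √[1 + d²p(1 − p)], while the true SE stays put because sex is balanced. With p = 0.68 female:
- d = 0.5: √(1 + 0.25 × 0.2176) = 1.027; rejection 2[1 − Φ(1.645 × 1.027)] = 0.091.
- d = 0.8: √(1 + 0.64 × 0.2176) = 1.067; rejection 0.079.

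The simulation gave 0.092 and 0.079 against the nominal 0.10.

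**The case against.** The best counter-case is that the article condenses a fuller plan, that listing stratification factors is routine analysis-plan content, and that the text never says baseline ACT is among the responses. This stands in part. The free baseline is an inference from the listed terms and the interaction test. Silence on sex alone would carry little weight. The covariate rule, however, is printed, and an analysis plan that follows it inherits it. If baseline is not a response, baseline ACT is simply unadjusted, and precision is still lost.

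A reader might infer more than the document supports:

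- **That the primary estimates swing with chance imbalance.** Step 4 shows otherwise. The rule adds a covariate and mentions no time interaction, so with complete data the tested terms do not move.
- **That the rule inflates type I error.** The simulation found it close to nominal.
- **That the model changes in 40-64% of trials.** Those figures count flags, not variables that also meet the correlation condition.
- **That leaving out sex invalidates the standard errors.** It costs nothing unless sex predicts change, and then the test is conservative.
- **That random intercepts give wrong standard errors by a known amount.** The document gives no visit covariance from which to establish that. A different covariance structure is a modelling preference and not part of this point.

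**Conclusion.** The point holds as a matter of precision and prespecification. Under the inferred reading, adjusting for baseline ACT lowers the variance of the 3-month contrast by about 4-10% with truncation at entry, roughly 2-5% of the standard error. It lowers it by 20-30% if visit variances are equal and the correlation is 0.4-0.6. Because the entry criterion does restrict baseline ACT, the lower range is the more cautious one to plan on. Both ranges rest on assumed means, SDs and correlations. The imbalance rule is incomplete as printed and seldom recovers precision. Adding sex helps only if sex predicts change in ACT, where its omission makes the component tests somewhat conservative. That runs against the plan's stated wish not to miss a contributing component. The change is worth making because it is cheap, not because the planned analysis would be invalid.

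**What to change.** Delete the imbalance-test rule and prespecify baseline ACT and sex in the primary model, in one of two forms:

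- 3, 6 and 12 months as outcomes, with baseline ACT and sex as covariates. Components are then tested on their effects at the follow-up visits, so the sentence on interactions with time needs matching wording. The 4-10% figure was derived for this form.
- All four visits as outcomes, with component effects set to zero at baseline, and sex entered with its interaction with time.

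Any further covariates should be named in advance for their expected prognostic value. The cost is a few extra parameters and a wording change. Sex must be known in order to stratify, and ACT is already measured at baseline.
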